## Methods

### Study design

This is a Type II hybrid effectiveness-implementation two-arm cluster-randomised controlled trial comparing Left Write Hook (intervention) to trauma-informed non-contact boxing-only (control). The primary effectiveness outcome measure will be self-efficacy at the primary endpoint of postintervention (8 weeks). Alongside the Left Write Hook programme, we aim to concurrently assess the implementation of ‘champion training’, a Trauma-Informed Writing and Boxing Facilitation programme for new Left Write Hook facilitators. The primary implementation outcome will be fidelity of intervention training and delivery of both the Left Write Hook and the boxing-only conditions within the trial, across different facilitators and sites. Fidelity refers to the degree to which an intervention or programme is delivered as intended.^60^ A hybrid trial design is appropriate for our research as it evaluates both effectiveness and implementation outcomes, accelerating the potential for broader implementation.^63^

### Study aims

In this study, we aim to evaluate the effectiveness of the Left Write Hook programme in improving self-efficacy (primary effectiveness outcome), and, subsequently, mental health and modifiable indicators for chronic disease (secondary effectiveness outcomes) in adult survivors of child sexual abuse and other gender-based violence. We dually aim to determine the fidelity of a train-the-champion implementation strategy for intervention training and delivery (primary implementation outcome).

### Study setting

Trial sites will be local community or health services. We anticipate 3–5 trial sites, each hosting a minimum of one intervention and one control group.

#### Site recruitment

Sites will be recruited from public mental health services and not-for-profit organisations which support trauma survivors in the state of Victoria, Australia. For inclusion, sites must consent to cluster randomisation of participants within their site, agree to advertise the trial to their service users and provide a site liaison who will work with the research team to manage intervention delivery and complete a semistructured interview to evaluate implementation outcomes at trial end. There is no minimum number of participants that each site must provide. Programme facilitators will travel between sites to deliver the programme. Equipment has been designed to be portable for ease of movement between sites.

#### Participant recruitment

Trial participants will be adults (n=150) recruited via participating sites (ie, government and not-for-profit health services with a dedicated trauma support service) alongside online advertisements. A documentary detailing the development of Left Write Hook will also raise public awareness of the intervention,^64^ and flyers advertising the trial are displayed at cinemas screening the film. Following input from lived experience advisors and in line with principles of trauma-informed care,^26^ we have deliberately kept our inclusion criteria broad to ensure individuals maintain agency over their participation. To be included in the trial, participants must be 18 years or older, female-identifying or gender diverse, self-report a history of child sexual abuse or gender-based violence, including family violence, and be willing to provide contact details for their GP (General Practitioner) to enable the research team to make the GP aware of participation and to coordinate support if needed during participation. For the purposes of this study, the term ‘gender-based violence’ is inclusive of any experience of sexual violence or any physical, sexual or emotional violence from an intimate partner or family member in either adulthood or childhood. Exclusion criteria are high levels of suicidality in need of more crisis management, evaluated by a clinical psychologist and informed by the Suicidal Ideation Attributes Scale.^65^ All participants complete an intake interview with a clinical psychologist trained in risk formulation to collaboratively decide whether to participate. During the interview, the clinical psychologist queries physical health, mental health and situational factors (eg, ongoing violence) that may impact an individual’s safe participation. Safe participation means that involvement in the programme does not negatively impact an individual’s physical or mental health, does not place them or others at risk of harm and does not interfere with ongoing evidence-based treatments (eg, participants undergoing EMDR may choose to delay participation until treatment is complete to avoid potential interference from the expressive writing component of Left Write Hook with memory reprocessing). Where safety concerns are identified, the clinical psychologist may recommend that the individual delay participation until their circumstances are more stable; for example, once an injury is healed or external supports are in place. We initially preregistered inclusion criteria to include a requirement for a letter of support from the GP; however, we decided to remove this to enhance equity of participation (ie, in situations where the GP has been non-responsive). Instead, the participant will provide contact information for their GP and any other mental health professionals, with consent sought for them to be contacted if safety concerns arise in the intake interview or during the programme. As per our risk management protocol (see online supplemental Materials for full protocol), if the trial team identifies safety concerns, the GP or other health professionals will be contacted to confirm that the participant can take part safely and to ensure continuity of care. Where the GP or other health professionals involved in the person’s care express concerns about safety of participation, this will be discussed with the individual so that they are aware of possible risks related to their involvement and they will be invited to participate once their professional supports advise it is safe to do so.

### Procedure

To determine eligibility, potential participants complete an intake interview with a clinical psychologist prior to enrolment in the trial. All enrolled participants will complete assessments at preintervention (0 weeks), postintervention (8 weeks) and at 1 month following the completion of the intervention (12 weeks). Self-report assessments can be completed at home or on the phone with a member of the research team. In-person assessments are taken by the programme facilitator immediately prior to the first session and immediately following the final session. Detailed information about the methodology and timing of assessments is outlined in figure 1. Eligible participants will not have to pay for the Left Write Hook or boxing-only programmes. Left Write Hook is currently accessible in the community (delivered via a survivor-led charity) through a suggested ‘pay what you feel’ donation of up to AUD$450 to the Left Write Hook charity. Participants also receive a AUD$20 Giftpay voucher for each of the three online assessments they complete. Those in the boxing-only condition will be offered participation in the Left Write Hook programme at the end of the trial.

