### The current study

We aim to complete a hybrid effectiveness-implementation cluster-randomised control trial to both evaluate the impact of Left Write Hook on the self-efficacy of adult survivors of child sexual abuse and gender-based violence and concurrently develop and evaluate the fidelity of a train-the-champion implementation strategy for delivery in new settings. Alongside assessing effectiveness, an implementation evaluation is essential to establish to inform intervention scalability as well as address apprehensions around peer support programmes for survivors.^27^ We hope that insights into the implementation of Left Write Hook will help to inform training and delivery models of peer-led interventions for survivors more generally.

We compare Left Write Hook to a control group of trauma-informed non-contact boxing only, delivered by a personal trainer (rather than a fellow survivor), akin to the type of current evidence-based programme survivors can access in the community. The resource (ie, both interventions able to be delivered by non-psychologists) and time commitment for participants were matched between trial arms. We hypothesise that those completing Left Write Hook will experience a greater improvement in self-efficacy, relative to the control intervention, at postintervention.

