### Intervention

#### Left Write Hook

Left Write Hook is delivered via 8× weekly 2-hour group-based sessions in a local gym/sports centre or community room. Sessions are led by two paid peer facilitators: a lead facilitator, assisted by an assistant facilitator, both of whom are survivors themselves. All peer facilitators are paid in line with industry rates for casually employed facilitators of exercise-based interventions. Each session has two components: expressive writing and trauma-informed non-contact boxing. An outline of the full programme, including session themes, is shown in table 1.

**Table 1 T1:** Outline of Left Write Hook programme

Week	Theme	Primary session goal
1	Grounding	Help people feel comfortable in the space and instil participants with a sense of purpose and feeling of being grounded.
2	Balance	Teach participants how to channel their emotions through the boxing. Create a safe environment for difficult emotions.
3	Expression (fluidity)	Help guide participants through difficult emotions and help them feel comfortable expressing themselves through writing and boxing. Give participants a healthy outlet.
4	Lightness	To have participants feeling lighter and more accomplished. To have participants feeling confident with their boxing.
5	Taking back your power	To have participants feeling confident in their boxing capabilities. To give participants the ability to harness their power.
6	Fighting Back	Give participants the building blocks to defend themselves. Have participants feel confident with weaving and pad work. Have the participants understand and express healthy aggression.
7	Rewriting narratives	To have participants take back their personal power
8	Imagining futures	To have participants be ready for the next steps in life once the programme ends, whether their next step is to return, become a facilitator or leave with a more positive outlook on life moving forward.

Writing prompts reflect the theme of each session.

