The first hour involves participants writing to recovery-focussed prompts designed to reclaim their life narrative and encourage meaning-making (eg, ‘fighting back means…’), with the option of sharing with the group to encourage expression and validation. Writing prompts reflect the theme of each session. Participants are invited to write about anything that comes to mind for them in response to the writing prompts and session theme. While this means that they are not required to write about past trauma and may choose to write about any topic, participants do predominately choose to write about their experiences of trauma or its impact on them. Peer facilitators guide the expressive writing and also participate in the writing and sharing. Next, participants complete a 45-min trauma-informed non-contact group boxing session. Peer facilitators guide participants to connect with their body and locate an empowered state, carrying through the theme from the expressive writing to guide participants’ focus on stance, punch, direction and movement. Each session ends with 15 min of grounding and reflections. Details on how the principles of trauma-informed care are embedded within the programme are outlined in table 2.

**Table 2 T2:** Examples of trauma-informed considerations across interventions and research procedures

Programme element	Trauma-informed principle(s)^25^
*Intake*	
Use inclusive and easy to understand language	Empowerment, voice and choice
Provide clear and detailed information on what the programmes involve	Safety, trustworthiness and transparency
Collaborative decision-making with potential participants regarding programme suitability at this time	Empowerment, voice and choice
Establish confidentiality and safety regulations	Safety, trustworthiness and transparency
Let survivors choose to share or withhold	Empowerment, voice and choice
*Both Left Write Hook and boxing-only interventions*	
Female or gender-diverse facilitators	Empowerment, voice and choice
All facilitators trained in trauma-informed facilitation	Safety, trustworthiness and transparency
Venue selection (accessibility, private space, limiting mirrors, quiet break-away space)	Safety
Invitational facilitation style to promote agency and choice	Safety, empowerment, voice and choice
Facilitators complete in-person research assessments, not trial staff	Safety, trustworthiness and transparency

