#### Active control: boxing-only

Participants randomised to control will complete 8× weekly group sessions of trauma-informed non-contact boxing, without writing and without a specific focus on empowerment, to control for the positive effects of exercise on self-efficacy. Each week, participants will complete a 45-min group boxing session, led by a boxing instructor (ie, intervention is not peer-led) at the same sites as the intervention arm. This replicates the type of trauma-informed exercise class that survivors could access in their local community. Boxing was selected as the exercise modality based on consumer input that identified it as the most acceptable exercise option for an active control, particularly in the context of consenting to randomisation. The control group therefore represents trauma-informed exercise options as usual, without three unique components of the Left Write Hook intervention: the peer-led nature of intervention, expressive writing and the focus on empowerment that links from the expressive writing to the trauma-informed non-contact boxing component to encourage expression through physical movement. Trauma-informed considerations for the boxing-only group are outlined in table 2.

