#### Effectiveness

Evaluation of effectiveness will be conducted at the individual level (participant and facilitator, including withdrawals) to determine the impact of the programme on psychosocial and physical health outcomes. Participants who withdraw from the study will still be invited to complete outcome measures. All outcome measures are outlined in the online supplemental materials (Table S1). The primary effectiveness outcome is self-efficacy, measured by participant score on the General Self-Efficacy Scale.^53^ Secondary effectiveness outcomes will include complex PTSD symptoms, trauma-related cognition (trauma memory quality and post-traumatic cognitions) and indices of physical health (strength, flexibility, aerobic fitness and balance). Exploratory effectiveness outcomes include depression and anxiety, social connectedness, mental well-being, quality of life, health behaviours (exercise habits, smoking and vaping frequency, alcohol intake and use of health resources) and physical health (blood pressure, chronic pain, sleep quality and stress hormones). Self-report measures will be administered online via Qualtrics, either at home in a comfortable environment, via phone call with a member of the research team or at the gym/sports centre with the support of a facilitator. Due to logistical constraints, preintervention in-person assessments (physical fitness, blood pressure and hair sample) will be completed immediately prior to the commencement of the first Left Write Hook or boxing sessions at the sport centre by an unmasked programme facilitator, with responses recorded via Qualtrics. Hair samples indexing stress hormones (see online supplemental Table S1 for details) will be collected by the programme facilitator, trained in collection procedure by a member of the research team. Samples will be wrapped in aluminium foil and stored in a plastic ziplock bag and kept at room temperature in a locked cabinet until analysis, as per recommendations in the field.^68^

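### Fitness and blood pressure are measured before exercise at baseline but straight after a boxing session at follow-up, so within-arm change mixes training with acute exercise effects; the arm contrast is protected only if recovery time is equal

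*Protocol article*

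**What the plan says.** The Procedure section fixes both time points: "In-person assessments are taken by the programme facilitator immediately prior to the first session and immediately following the final session". The Effectiveness section (under Outcome measurement by RE-AIM dimensions) lists the content and repeats the baseline half: "preintervention in-person assessments (physical fitness, blood pressure and hair sample) will be completed immediately prior to the commencement of the first" sessions of either programme. The same section makes strength, flexibility, aerobic fitness and balance secondary outcomes and blood pressure an exploratory one.

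The session structure is given arm by arm:

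- **Left Write Hook, overall length:** "Left Write Hook is delivered via 8× weekly 2-hour group-based sessions in a local gym/sports centre or community room".
- **Left Write Hook, order of activities:** "The first hour involves participants writing to recovery-focussed prompts"; then "Next, participants complete a 45-min trauma-informed non-contact group boxing session"; then "Each session ends with 15 min of grounding and reflections".
- **Control (Active control: boxing-only):** "Each week, participants will complete a 45-min group boxing session, led by a boxing instructor". No closing period is mentioned, and none is ruled out.

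The section The current study says that the resource and "time commitment for participants were matched between trial arms".

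The Statistical analysis plan section analyses continuous secondary and exploratory outcomes like the primary one, that is, as the difference between arms in mean change from preintervention. Paired t-tests are reserved for the hair samples.

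**The concern.** Time point and exercise state are completely confounded. No one has exercised in a session before the baseline measure, and everyone who attends the final session has boxed shortly before the follow-up measure. Fatigue, warm muscles and post-exercise circulation can all move strength, flexibility, aerobic, balance and blood-pressure readings, in directions that may differ by test. No model can separate these from eight weeks of training, because no participant is measured in the same state twice.

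Two readings are at stake. The first is any statement that fitness or blood pressure changed within an arm over the programme. The second is the arm contrast, if participants in the two arms have had different lengths of recovery when they are measured.

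**Working it through.** **1. Reproduce the stated session length.** Left Write Hook: 60 min writing + 45 min boxing + 15 min grounding = 120 min, which matches the stated 2 hours. Boxing therefore ends 15 min before the session does. Control: 45 min of boxing is all that is described.

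**2. Exercise state at each measurement, as described.**

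| | Baseline | Follow-up: boxing in the session just ended | Follow-up: time from end of boxing to end of session |
|---|---|---|---|
| Left Write Hook | before any session | 45 min | 15 min |
| Control | before any session | 45 min | not stated; 0 min only if there is no closing period |

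**3. What enters each quantity.** Let T be the true training change in an arm, A the acute shift in a measure at the end of boxing, and g(t) the share of A still present after t minutes, with g(0) = 1. Suppose A is the same in both arms, since both box for 45 min.

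- Within-arm change = T + A × g(t).
- Arm contrast (Left Write Hook minus control) = (T_L − T_C) + A × [g(t_L) − g(t_C)].

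The within-arm change is shifted whenever g(t) is above zero. The contrast is shifted only when t_L and t_C differ; if they are equal, the bracket is zero.

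**4. Illustration of the bracket if control has no closing period.** The documents give neither A nor its rate of decay. Assume g(t) = exp(−t/τ), with t_L = 15 and t_C = 0. The bracket is then exp(−15/τ) − 1:

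- τ = 10 min: 0.22 − 1 = −0.78, so the contrast shifts by −0.78A.
- τ = 30 min: 0.61 − 1 = −0.39, so −0.39A.
- τ = 60 min: 0.78 − 1 = −0.22, so −0.22A.

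A may be positive for one test and negative for another, so the shift could favour either arm. This shows how the bias would behave; it is not an estimate for this trial.

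**5. Side by side: matched time.** Eight sessions of 2 hours are 8 × 2 = 16 hours. Eight sessions of 45 minutes are 8 × 45 = 360 min = 6 hours. These figures do not fit the statement that time commitment was matched. Either the account of the control visit is incomplete or that statement is wrong; the text does not show which.

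**The case against.** **The planned analysis is between arms.** Both arms box for 45 minutes before the follow-up measure, so a shared acute effect drops out, and no within-arm test of fitness or blood pressure is planned. This stands, and it limits the firm part of the point to the pre-post change.

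**The unequal recovery time is read from silence.** A reader might infer that participants are measured 15 minutes after boxing in one arm and 0 minutes after in the other, and hence that the contrast is biased. The documents do not support that as a fact. The control description does not say that there is no cool-down, and the matched-time statement suggests that the control visit may contain more than is described. With groups of 8–10 assessed by facilitators, the gap will also vary by person unless all are tested at once, so no single number holds for an arm. The arm bias is therefore conditional.

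**The detail may be elsewhere.** The Procedure section refers to Figure 1 for assessment timing, and Table S1 covers outcome measurement; neither is shown. Either could set a rest period or a test order, and their absence here is not a fault. But the article states the rule itself, before the first session and immediately after the last. A rest period would shorten the mismatch without making the two time points alike. The listed study limitations mention unmasked assessors, not this timing.

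**The primary outcome is untouched.** Correct: self-efficacy is self-reported and is not one of the in-person measures.

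**Conclusion.** The point holds as a stated scheduling rule that makes exercise state differ between baseline and follow-up. It affects four secondary fitness outcomes and exploratory blood pressure, for every participant measured as scheduled. Within-arm changes in these measures cannot be read as training effects.

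For the arm contrast the conclusion is conditional. If recovery before measurement is equal and the acute effect is similar in both arms, the contrast is largely protected. If control has no closing period, the contrast carries the part of the acute effect that differs between arms. Its size and direction cannot be computed from the documents; the range of 0.22A to 0.78A in size rests on an assumed exponential decay and an unknown A.

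This is worth correcting because the remedy is cheap. It does not threaten the primary result.

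**What to change.** For the remaining groups, take the postintervention fitness and blood-pressure measures immediately before the final session, in the same order and pre-exercise state as at baseline, in both arms. This uses the same kind of slot, staff and venue as the baseline assessment.

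If measurement has to stay after the session, set one fixed rest interval, the same in both arms, and record the actual time since boxing. That protects the arm contrast but leaves the pre-post change confounded.

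Recruitment opened in September 2024, so some groups may already have been measured under the current rule. Make the switch in both arms at the same time within each site, so that timing does not become confounded with arm. Flag each group's assessment timing and report a sensitivity analysis by timing. For completed groups, use only timing that was captured when it happened, such as Qualtrics time stamps if available; it cannot be recorded afterwards.

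Reconcile the matched-time statement in The current study with the session descriptions under Left Write Hook and Active control: boxing-only, and state whether the control session has a closing period.

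Cost: a procedural amendment with no added visit. The follow-up measure would reflect seven completed sessions instead of eight, and two timing conditions would be mixed across the trial.
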